## Abstract

**Background:**

German hospitals are legally obliged to implement digital patient portals within the next years. Systematic reviews show that the use of patient portals may be associated with improved patient-centeredness and workflows. However, mandatory digital healthcare innovations are sometimes not used by the target group as planned or even completely rejected. Based on Roger's theory of innovation diffusion, it can be assumed that the time factor is of particular importance for the adoption of the patient portal. The aim of the project is to assess determinants of patient portal adoption and to examine whether Roger’s theory can be confirmed.

**Methods:**

The project investigates the use of the patient portal in three different clinics of a large academic teaching hospital in Germany using a longitudinal study design with three cross-sectional time points (pre, post, post). Doctors and patients are surveyed about factors that predict the use of the patient portal and whether the strength of these factors changes over time. They are also interviewed about possible barriers they experience when using the patient portal or about the reasons why the patient portal is not used. Regression models and content analyses are used to answer the research questions.

**Discussion:**

Determinants of patient portal use will be discussed under the light of the temporal component of Roger's theory. At the same time, it is expected that some determinants will remain unchanged over time. Identifying determinants independent of time allows targeting the groups, enabling specific communication strategies to empower these groups to use the patient portal, contributing to an equal health care system.

**Trial registration:**

The study was prospectively registered in the German register of clinical trials (DRKS00033125) in May 2024.

Contributions to the literature
Literature shows that digital innovations are sometimes not adopted by the target groups despite being implemented to a high standard.Roger's theory of the diffusion of innovations describes different groups of people (e.g. innovators and laggards) who are ready to adopt an innovation at different times. This study analyses the adoption of a patient portal against the background of the theory described.The results will contribute factors to the literature that influence the adoption of a patient portal depending on the time factor and provide empirical findings on the transferability of the theoretical models to the practical example of patient portals.

## Background

### Relevance

The German healthcare system is hardly digitized. In the last representative European benchmark, Germany was ranked 16th out of 17 compared countries (Bertelsmann [5]). This is especially noticeable for the inpatient setting. In the latest national digital maturity survey, German hospitals scored an average of just 33 out of a possible 100 points [1]. Several context-specific factors can be considered to explain this. First, the German healthcare system is characterized by self-administration, which goes hand in hand with a high level of bureaucracy [7]. Secondly, the reimbursement system is dualized, with insufficient public funds for increasing investment requirements, leading to an investment backlog, particularly in digital infrastructure [11]. Not only the Covid-19 pandemic, but also excessive increases in expenditure have highlighted the need for the healthcare systems digital transformation and have led to legal action. In a series of laws (PDSG, KHZG), politics have now mandated hospitals to implement various digital innovations, while simultaneously providing significant financial resources to cover these investments.

A past example is the obligation for statutory health insurances to offer their patients a voluntary electronic health record or to process medical prescriptions electronically between prescribers and dispensing pharmacies. A scenario still to come for German hospitals is the mandatory implementation of patient portals (PP) for a digital admission, treatment and discharge management to enable a digital exchange of information between service providers and recipients by the beginning of 2025 (KHZG §19 (2)). Due to the wide range of possible functionalities (e.g. appointment booking, record access or health diary), PP offer numerous advantages for patients and organizations [12]. Systematic reviews indicate that PP can enhance patient-centered care and improve healthcare processes [2, 21, 29]. Patient-centered care, in this context, focuses on empowering patients to take a more active role in the treatment process and view themselves as partners in their care [15, 18]. Regarding healthcare processes, there is evidence for a decrease in general information requests [16] and specific telephone contacts [17, 34]. Furthermore, it is noted that documents provided by patients through the PP can enrich the healthcare process with crucial information [3].

To achieve the potential improvements, offering a PP alone is not sufficient. The given example of the obligation for statutory health insurers to offer their patients a voluntary electronic health record illustrates this. These electronic health records must be actively requested by each individual patient in order to be set up (opt-in). In 2019, before the law came into force, 62% of the patients with statutory health insurance declared their willingness to use the electronic health record [6]. However, only 0.5% had actually requested it by the end of 2021 [28]. The aim of the project presented is to prevent the example described above, for the PPs still to be implemented, that a politically enforced digital innovation is not utilized. It is therefore important to understand which factors influence the adoption of the PP and which barriers are experienced, in order to actively empower and support disadvantaged groups of people to use the PP.

The framing use case for the research project is the PPs tool of digital anamnesis collection (DAC). DAC refers to the approach of postponing the medical history taking before the actual appointment. With the help of the PP, the patients can use their computer or smartphone to enter their medical history, allergies, etc. at home at their own pace or with their relatives’ support. This is meant to improve the quality of the information, which is also available for the physician when planning the appointment and therefore allows the consultation to be more efficient and target-oriented [27]. On the other hand, the DAC is characterized by the fact that it must be equally used by both, patients but also the physicians in order to realize its potential to improve healthcare delivery, making it even more important to understand the described factors, influencing the adoption of the PP. Of particular relevance is the fact that all German hospitals will be required to offer such DAC in the future.

### Theory

Roger's theory of the diffusion of innovations (DOI) serves as a framework for investigating the determinants of the adoption of the PP [25]. The DOI describes various factors (person-related or innovation-related) that influence when and whether an individual is willing to use an innovation. In that matter, the dimension of time is of particular relevance. In this temporal sense, the DOI distinguishes five types of "innovation adopters" (*innovators, early adopters, early majority, late majority, laggards*) who adopt an innovation at different points in time (Fig. 1). The *innovator* type, a very small group, is interested in using innovations as early as possible, while the *laggard* is unwilling to use the innovation until a long time has passed, if the innovation can still be called an innovation for the *laggards*, in view of the time that has passed since its introduction until the *laggard* type is ready to adopt.

**Fig. 1 Fig1:**
[figure not shown]
Temporal diffusion of innovations [25]

Assuming, for example, that the individual’s digital literacy is a possible determinant of PP usage, it is expected that individuals with a markedly high level of digital literacy will adopt the PP particularly early (thus corresponding to the *innovators* type). However, the relevance of high digital literacy as a determinant of PP usage decreases over time. Accordingly, at a later stage, individuals with lower digital literacy would also adopt the PP (e.g. representing the *late majority* type). Regarding the research topic of PP, it is unclear whether the DOI can be applied. Even though one study has already shown that, following the DOI, the proportion of users of the PP increased slowly but steadily over time, implying an expected transition from only *innovators* among the users to additional *early adopters* among the users at a later date [33]. However, it is still unexplored, whether the relevance of potential determinants weakens over time or remain time constant. At the same time, it is uncertain whether and how the strength of the determinants or the extent of the expected weakening of these determinants is related to the clinical context (e.g., outpatient/inpatient) in which the PP is offered for use. In addition, there is no conclusive evidence as to whether and how the implementation of a PP and particularly the DAC affects documentation and treatment quality.

### Hypotheses & research questions

All research questions explicitly addressed in the research project are listed in Table 1.

**Table 1 Tab1:** Dedicated hypotheses & research questions

Quantitative Hypotheses (A) Determinants of Patients PP Usage	
A1	The relative proportion of patients using DAC with low digital literacy increases over the observation period
A2	The relative proportion of patients using DAC with low health literacy increases over the observation period
A3	The relative proportion of patients using DAC with low technology acceptance increases over the observation period
A4	Patients planned for inpatient treatment are more likely to use DAC than patients receiving acute outpatient care
A5	Patients who are frequently treated in the hospital (either outpatient or inpatient) are more likely to use DAC than those who are less frequently treated
Quantitative Hypotheses (B) Determinants of Physicians PP Usage	
B1	The relative proportion of physicians using DAC with low digital literacy increases over the observation period
B2	The relative proportion of physicians using DAC with low technology acceptance increases over the observation period
Qualitative Research Question (C) Barriers to PP Usage or Reasons for Non-Usage	
C1	What are the patient-related reasons for non-usage and barriers during the usage of DAC over time?
C2	What are the physician-related reasons for non-usage and barriers during the usage of DAC over time?
Exploratory Research Question (D) Actual PP Usage	
D1	How does the documentation of medical history change over time with the utilization of DAC through the PP?
Exploratory Research Question (E) Changes in Administrative Data	
E1	What changes occur in the data collected for administrative purposes after the introduction of the PP?

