## Methods / design

The study follows a longitudinal triple cross-sectional design (pre-post-post). It is based on three consecutive data collection phases, conducted in three clinics of a large academic teaching hospital in Germany. Data will be collected in each of the three clinics 2 months before the implementation (t0), as well as 6 months (t1) and 12 months (t2) after the implementation of the PP. Each of the three clinics has an eight-week period allocated for data collection to achieve the targeted case numbers described below. Quantitative data from surveys of patients (A) and physicians (B), qualitative data from interviews with patients and physicians (C), as well as medical history documentation (D) and administrative data from a participating clinic (E) are used to answer the research questions (Fig. 2). Each of the research questions (A) – (E) will be presented in detail in the following, including detailed case number calculations or sampling strategies.

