**Fig. 2 Fig2:**
[figure not shown]
MAiBest study design

A)Analysis of determinants of patients PP usage

The trend survey at the three measurement time points (t0; t1; t2) allows for the depiction of determinants of PP usage and the expected changes in these determinants over time. The t0 survey captures the clinic-specific heterogeneity of patient-related determinants for PP use and enabling an adjustment of the trend analysis for these baseline values from t0. This facilitates the examination of trends within each clinic and allows for comparisons between the three clinics. Patients treated in the three clinics at the three measurement time points (t0; t1; t2), whether inpatient or outpatient, will receive a paper-based questionnaire with additional, optional access to a digital version. These questionnaires include items measuring patient-related determinants and, additionally, usage behavior in t1 and t2. The patient surveys are based on existing and validated scales (e.g. digital literacy [26], technology acceptance [20], or if not possible, on items developed according to methodological standards [23]. Additionally, socioeconomic and sociodemographic factors (e.g., age, gender, education, income) are recorded for later adjustment.

The sample size calculation results in a required rounded *N* = 200 patients per measurement time point per clinic (pooled total *N* = 1800). This is based on an assumed weak effect size for Cohen's D of 0.2 with 80% power and a significance level of 0.05 for a (1) two-sided independent two-sample t-test for the comparison between clinics at each measurement time point (total *N* = 393 at each time point for the comparison between two clinics, rounded *n* = 200 per clinic) and (2) for the comparison within the clinic across measurement time points in a two-sided paired t-test (required *n* = 198 per time point). The data analysis is performed using descriptive and inferential statistics, adjusting for previously collected socioeconomic and sociodemographic characteristics, conducted with the statistical software SPSS^©^.

B)Analysis of determinants of physicians PP usage

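### A1–A3 fix the share of low scorers among DAC users, which can rise although the determinant's odds ratio for use is unchanged; the stated question needs a score-by-wave term

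*Protocol article*

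**What the plan says.** The Abstract (Methods) says that doctors and patients are surveyed about factors predicting portal use and "whether the strength of these factors changes over time". The Theory part of the Background gives the expectation for digital literacy, that "the relevance of high digital literacy as a determinant of PP usage decreases over time", and names the gap: "it is still unexplored, whether the relevance of potential determinants weakens over time or remain time constant". The same section cites a study in which "the proportion of users of the PP increased slowly but steadily over time".

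Table 1 turns this into A1: "The relative proportion of patients using DAC with low digital literacy increases over the observation period". A2 (health literacy) and A3 (technology acceptance) are worded alike.

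Methods / design describes three cross-sectional waves. Part A says of the patient surveys: "These questionnaires include items measuring patient-related determinants and, additionally, usage behavior in t1 and t2". The t0 wave supplies clinic-level baseline values for adjustment, and social and demographic factors are recorded as covariates. The Abstract announces regression models, and part B mentions in passing that the patients' dependent variable is binary actual use. Part A sizes the patient survey at 200 per clinic and wave, from t-tests on a mean difference of d = 0.2.

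**The concern.** Whether a determinant weakens is a question about the association between score and use, compared between waves. It needs users and non-users at each wave. A1–A3 name another quantity: the proportion of low scorers within the group of users. That proportion combines three things: how strongly the score relates to use, how many patients use DAC at all, and how many low scorers were surveyed in that wave. The protocol leads one to expect the second to change, and independent cross-sections allow the third to change.

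The distinction bears on the conclusions. The Abstract's Discussion intends to target groups identified by determinants that do not depend on time, and the Discussion section rests generalisability on the time-constant ones. If a constant determinant is read as weakening because the user share rose, the group that needs support may be left out.

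**Working it through.** **Inputs.** From the protocol: use recorded at t1 and t2 only; 200 patients per clinic and wave, so 3 × 200 = 600 per wave; d = 0.2, 80% power, two-sided 0.05. The protocol gives no figure for uptake, share of low scorers or odds ratio, so all of these are assumptions below.

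**1. The printed sample size.** The paired t-test at d = 0.2 gives 198.2, matching the printed 198. The two-sample formula gives 2 × (1.960 + 0.842)² / 0.2² ≈ 393 per group; the protocol prints 393 as the total for two clinics. That is a separate matter. What counts here is that both calculations concern a difference in means, and neither concerns a change in association.

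**2. Uptake alone.** Let π be the share of low scorers surveyed, and u_L and u_H the use in low and high scorers. The low share among users is

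S = π·u_L / (π·u_L + (1 − π)·u_H).

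Take π = 0.40 and hold the odds ratio (low against high) at 1/3:

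| Overall uptake | u_L | u_H | S |
|---|---|---|---|
| 10% | 4.9% | 13.4% | 19.6% |
| 30% | 17.3% | 38.5% | 23.0% |
| 50% | 34.0% | 60.7% | 27.2% |
| 70% | 56.1% | 79.3% | 32.0% |

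The share rises throughout while the odds ratio stays at 1/3.

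**3. Case-mix alone.** Hold u_L = 0.20 and u_H = 0.50 in both waves:

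- π = 0.30: 0.06 / (0.06 + 0.35) = 14.6%
- π = 0.40: 0.08 / (0.08 + 0.30) = 21.1%

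Nobody's probability of use has changed.

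**4. The reverse error.** At 30% uptake, let the odds ratio weaken from 1/3 to 1/2 while π falls from 0.40 to 0.30. S falls from 23.0% to 20.5%, so a real weakening looks like its opposite.

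**5. The other reading of A1.** If the wording means uptake among low-literacy patients, the quantity is u_L. In step 2 it goes from 17.3% to 34.0% between 30% and 50% uptake at the same odds ratio, so it also follows general uptake.

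**6. Scale.** Dividing through by u_H gives S = π·RR / (π·RR + 1 − π), with RR = u_L/u_H. At fixed case-mix the share therefore tracks the risk ratio. Between 30% and 50% uptake in step 2, the risk ratio moves from 0.45 to 0.56 and the risk difference from 21.2 to 26.7 points, while the odds ratio is constant. Whether the determinant weakened depends on the scale, so the hypothesis must name one.

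**7. Power for the interaction.** Assume 600 per wave, a standard normal score, no covariates and a two-sided 0.05 test. With I₁ and I₂ the expected information per patient on the slope at each wave, SE² = 1/(600·I₁) + 1/(600·I₂) and power ≈ Φ(ln(OR₁/OR₂)/SE − 1.96). The log changes are ln(2.0/1.2) = 0.511, ln(2.0/1.4) = 0.357 and ln(2.0/1.6) = 0.223.

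| Uptake t1 to t2 | SE (middle column) | OR per SD 2.0 to 1.2 | 2.0 to 1.4 | 2.0 to 1.6 |
|---|---|---|---|---|
| 10% to 20% | 0.180 | 81% | 51% | 23% |
| 22% to 37% | 0.141 | 95% | 71% | 34% |
| 30% to 50% | 0.133 | 97% | 77% | 38% |
| 50% to 70% | 0.132 | 97% | 77% | 38% |

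Example, second row: 0.357/0.141 − 1.96 ≈ 0.56, and Φ(0.56) ≈ 71%.

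**The case against.** The strongest reply is that the protocol does not say A1–A3 will be tested by comparing user composition. It plans regression with binary use as the patient outcome, and such a model keeps non-users. Model detail is commonly left to an analysis plan that is not shown. This stands in part: the loss of non-users follows only from a literal reading of Table 1. But the hypotheses are printed here, and they fix a quantity other than the one the aim asks about.

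The planned covariate adjustment may reduce a case-mix shift, since age and education plausibly go with literacy. It does not remove the uptake effect. Adjustment to t0 cannot correct a change that arises between t1 and t2.

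The uptake effect is specific to a constant odds ratio; with a constant risk ratio and fixed case-mix, the share would not move. This stands.

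Three stronger readings are tempting and not supported:

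- A reader might infer that A1 would be falsely confirmed when uptake rises. If the user share rises, A1 as worded is true. What fails is the further step to a weakened determinant. How often a test would mislead depends on the test chosen and on the adjustment, neither of which is specified.
- A reader might infer that counting users only cuts power from 80% to 19%. The 19% rests on an assumed 30% uptake (60 users per clinic and wave). The printed 80% is not attached to A1–A3, and all 200 per clinic give only 51% in a two-sample t-test at d = 0.2. The comparison would mix in the separate sizing issue.
- A reader might infer from the word low that scores will be cut into categories. No cut-off or dichotomised analysis is stated.

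**Conclusion.** The point holds as a mismatch between the stated question and the wording of A1–A3. The low-scorer share among users can rise by several percentage points with no change in the odds ratio: 4.2 points (23.0% to 27.2%) from uptake alone, or 6.5 points (14.6% to 21.1%) from case-mix alone, under the assumed values. It can also fall while the odds ratio weakens. Reading the hypothesis as uptake among low scorers does not help. The sizes are illustrations; the direction of the uptake effect requires the odds-ratio scale, whereas the case-mix effect does not. It should be fixed: regression on binary use is already planned and non-users are surveyed, so the remedy is one of wording and model specification.

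**What to change.** Restate A1–A3 as: the association of digital literacy (A1), health literacy (A2) or technology acceptance (A3) with DAC use weakens from t1 to t2, on the odds-ratio scale.

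For each determinant, test this in the planned regression of binary use among all t1 and t2 respondents, pooled over clinics. Include the continuous score, wave, score-by-wave, clinic and the planned covariates. Report the odds ratio at each wave and the ratio of the two with its confidence interval. Keep the composition of users as a descriptive result.

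State that 200 per clinic and wave was derived for mean differences of d = 0.2 and not for this interaction, and give the interaction's power over a range of assumed uptake, as in the table above.

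The cost is three reworded hypotheses, one model specification and a short power statement; no further data are needed. The downside is that the restated power is likely less favourable than the printed 80% for small changes: for a fall in the odds ratio per SD from 2.0 to 1.6 it is 23% to 38% under the assumptions shown.

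### A1-A3 are worded as a rising proportion of low scorers among DAC users, but the only stated power (80%) is for a mean difference of d = 0.2 and does not apply to them as worded

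*Protocol article*

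**What the plan says.** In the protocol article, Background, Hypotheses & research questions, Table 1, A1 reads: "The relative proportion of patients using DAC with low digital literacy increases over the observation period". A2 and A3 repeat it for low health literacy and low technology acceptance. Each is a statement about a proportion, and no threshold for low is given.

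Methods / design, part A, gives the patient sample size: "required rounded *N* = 200 patients per measurement time point per clinic (pooled total *N* = 1800"). Its basis is an "assumed weak effect size for Cohen's D of 0.2 with 80% power and a significance level of 0.05", applied to two tests:

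- Between clinics: a "two-sided independent two-sample t-test for the comparison between clinics at each measurement time point", with "total *N* = 393 at each time point for the comparison between two clinics, rounded *n* = 200 per clinic".
- Over time: "for the comparison within the clinic across measurement time points in a two-sided paired t-test (required *n* = 198 per time point").

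Part A measures digital literacy and technology acceptance with validated scales and records usage at t1 and t2 only. It does not name the variable to which d = 0.2 refers. The Theory section describes the expected change as one where "the relevance of high digital literacy as a determinant of PP usage decreases over time". The abstract says regression models will be used, and part B states that the patient dependent variable is binary actual use.

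**The concern.** The hypotheses and the sample size use different effect measures. A standardised mean difference of 0.2 and a change in the share of respondents below a cut are different quantities, and power for one does not carry over to the other. Part A gives no power for a proportion, so A1-A3 as worded have no stated power.

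This affects the interpretation. A1-A3 are the patient-level tests of the theory over time. The Discussion intends to generalise determinants and barriers that prove constant over time. A non-significant A1, A2 or A3 would invite that label, and a reader would take the 80% as reassurance that a shift of the assumed size would probably have been seen. For the proportion, that reassurance has not been established.

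**Working it through.** **1. Reproduce the stated figures** (d = 0.2, two-sided 5%, 80% power; part A).

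- Independent t-test: n per group = 2(1.960 + 0.842)²/0.2² = 392.4, so 393. The exact t solution is 393.4, so 394 in whole patients.
- Paired t-test: n = (1.960 + 0.842)²/0.2² = 196.2. The exact t solution is 198.15, matching the stated 198.

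Both reproduce as figures for means. The 393 is a number per group, although part A labels it a total for two clinics. That is a separate fault, so the comparison below uses the n that really gives 80%.

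**2. Translate d = 0.2 into a proportion.** Assumptions, not in the article: normal score, equal SD, the whole distribution moves down by 0.2 SD, and a share p1 is low at the earlier time point. Then p2 = Φ(Φ⁻¹(p1) + 0.2).

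**3. Power of the two-proportion test**, equal independent groups of n:

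power = Φ[(p2 − p1 − 1.960·s0)/s1], where s0 = √(2·p̄(1 − p̄)/n), p̄ = (p1 + p2)/2, and s1 = √((p1(1 − p1) + p2(1 − p2))/n).

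For p1 = 0.50 and n = 394: p2 = 0.579, s0 = 0.0355, s1 = 0.0354, so power = Φ[(0.0793 − 0.0696)/0.0354] = Φ(0.27) = 61%.

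| Test | p1 to p2 | Power, n = 394 | Power, n = 600 | Power, n = 300 | n per group for 80% |
|---|---|---|---|---|---|
| Mean, d = 0.2 | – | 80% | 93% | 69% | 394 |
| Low = lowest 50% | 0.500 to 0.579 | 61% | 79% | 50% | 620 |
| Low = lowest 25% | 0.250 to 0.318 | 56% | 74% | 45% | 698 |
| Low = lowest 10% | 0.100 to 0.140 | 40% | 56% | 32% | 1049 |

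Here 600 is 3 clinics × 200 at one time point if every respondent uses DAC, and 300 is the same if half do. These are unadjusted comparisons.

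**4. The paired test that part A sized for change over time.** Take n = 198, the paired standardised difference at 0.2, and zero correlation. A median cut gives p2 = Φ(0.2√2) = 0.611. The discordant shares are 0.5 × 0.611 = 0.306 and 0.5 × 0.389 = 0.194, with sum 0.500 and difference 0.111. McNemar power = Φ[(0.111√198 − 1.960√0.500)/√(0.500 − 0.111²)] = 60%. Cuts at 30% and 20% give 58% and 53%. With correlation 0.5 the three figures are 48%, 46% and 40%.

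**5. A model in which the ranking reverses.** Assume a normal population in which the lowest quarter enters the user group at a relative rate of 0.2 at t1 and 0.5 at t2 (everyone else at 1), with 394 users per wave.

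- Cut at the step: low share 0.25 × 0.2/(0.05 + 0.75) = 0.063, rising to 0.25 × 0.5/(0.125 + 0.75) = 0.143. Power is about 96%.
- Mean score: 0.318 falling to 0.182, with SDs 0.827 and 0.919. SE = √((0.827² + 0.919²)/394) = 0.062, so power = Φ(0.136/0.062 − 1.960), about 59%.
- Cut at the median instead: 0.30/0.80 = 0.375 rising to 0.375/0.875 = 0.429. Power is about 33%.

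So the proportion wins only when the cut matches the place where change occurs.

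**The case against.** The strongest reply is that the article plans no dichotomised analysis. It gives no cut and no two-proportion test. It announces regression with binary use as the patient outcome, so continuous scores may well be intended, and how low is operationalised may stand in a document not shown. This is fair, and a missing cut is not the fault raised here. But the article's hypotheses are proportions and its only stated power is for means. A regression on the continuous score would test something other than A1-A3 as worded.

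Further objections stand in part:

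- A reader might infer that the article defines d = 0.2 on the full literacy score. It does not say so; that follows only from the use of Cohen's d, t-tests and validated scales.
- The 394 per group belongs to the between-clinic comparison, not to change over time. It is used here as a common yardstick; the paired version in step 4 shows a similar loss.
- A reader might quote the proportion test's power at 200 per clinic (36%, 32% and 23% for the three cuts) as the cost of splitting the score. Those figures also contain the 393 labelled as a total: at 200 per clinic even the independent mean comparison has only about 51%.
- Pooling helps. At 600 users per time point a cut near the median comes within a point of 80%. But part A did not size that comparison, and it requires every respondent to be a user.
- A reader might infer that a cut loses power at any n. Step 5 shows otherwise, and the Theory section's adopter types leave room for change concentrated among low scorers.

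**Conclusion.** The mismatch is on the page: the stated 80% refers to a standardised mean difference and does not apply to A1-A3 as worded. Its size is conditional. For a 0.2 SD shift in a roughly normal score, at the n that gives the mean 80%, the low proportion has about 61%, 56% or 40% power for cuts at 50%, 25% or 10%. Pooled with all 600 respondents as users, it has 79%, 74% or 56% against 93%, and less with fewer users. The shift model, the cut and the share of users are assumptions. The documents do not support the broader claims that dichotomising must lose power here, or that a score-based analysis would by itself restore 80%.

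**What to change.** - Reword A1-A3 so that the primary test compares the continuous score among DAC users at t2 with that at t1, the only time points with usage data. Keep the percentage of low scorers as a descriptive result.
- If wanted, add a regression of use on continuous score, time point and their interaction, as the test of whether the determinant weakens. State that this is a separate quantity.
- State that the 80% refers to a mean difference of d = 0.2 and covers neither the low proportion nor the interaction term. Neither proposed analysis was itself sized in part A. For orientation, an unadjusted pooled comparison of means at d = 0.2 needs 394 users per time point, or 394/600 = 66% of respondents.

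The cost is the wording of three hypotheses and a sentence on power; the scores are already collected. The downside is that a mean shift is harder to communicate than a percentage, and it may be less sensitive if change occurs only among the lowest scorers.
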